### 3.3.3. Community Strategies

#### 3.3.3.1 A generic model of the SMART2D Community Intervention

The SMART2D Community intervention arm comprises of the above outlined Health Facility strategies, as well as three main Community strategies: Community mobilization; Strengthening support from social and physical environment; and Community extension providing linkage between facility and community. Key elements for these strategies as well as specifications for generic tools are outlined in the table 6 below.

Table 6 SMART2D Community Strategies for the Health Facility + Community Arm

| **COMMUNITY STRATEGIES** | **KEY ELEMENTS** | **SPECIFICATIONS FOR TOOLS** |
| --- | --- | --- |
| **I. Community mobilization** | a. Messages on lifestyle and diabetes for community members / key stakeholders | i) One-pagers with key messages for: timely care seeking; risk monitoring & screening; healthy lifestyle |
|  |  |  |
|  |  |  |
| **II. Strengthen support from the environment** | a. Patient peer group program | i) Peer Group Guidelines with program topics and activities for monthly visits for one year |
|  |  | ii) Peer leader selection criteria |
|  |  | iii) Peer leader training protocol + Short guide to peer leader behaviors |
|  | b. Care Companion (CC) / Healthy Lifestyle Buddy (HLB) involvement | i) Booklet with CC / HLB role and task description |
|  |  |  |
|  | c. Promoting supportive physical environment | i) EPOCH manual and training slides  ii) PhotoVoice Training protocol and accompanying facilitator guidelines for PG’s. |
| **III. Community extension** | a. Community Link Team | i) Community Link Team guidelines  ii) Community Link Team training protocol |

*Community Strategy I: Community mobilization*

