Community mobilization is designed to raise awareness of type 2 diabetes and it’s prevention and management through healthy lifestyle, timely seeking of care and self-management of the disease. It will be used to raise interest in participation in the trial, and it will also help to create and strengthen advocacy for healthy lifestyle in the communities, thereby supporting the goals and activities of the Peer group program, Care Companions / Healthy Lifestyle Buddies and Community Link Team. Key messages for community mobilization will address knowledge gaps identified in the formative research, and they will be compiled in collaboration with relevant stakeholder organizations. Materials for community mobilization will include one-pagers with the key messages and/or visuals. They will be distributed in the Health Facility + Community arm at community screening events, and through partner organizations, Community Link Team, and Peer groups.

*Community Strategy II: Strengthening support from the environment*

This strategy includes strategies for both social and physical environment. ***Peer group program*** will provide an arena for emotional support, practical support and information exchange for individuals living with diabetes and pre-diabetes. Participants in the Health Facility + Community arm are referred to a peer group in their first motivational coaching session. Peer groups meet monthly at a local community venue under the leadership of appointed ***Expert patients*** and co-leaders selected from within each group. A generic ***SMART2D Peer Group Program manual*** (see Appendix) includes topics and activities for 1) building rapport; 2) setting agenda for the group; 3) working with topics selected by the group; 4) receiving and giving ongoing support; and 5) evaluation and adjourning. In addition to the activities, each group meeting will include a brief physical activity break and opportunity for unstructured discussion and sharing. Peer groups are also open for family members and Care Companions / Healthy Lifestyle Buddies. ***Selection criteria*** and recruitment of Expert patients as Peer group program facilitators are outlined in the ***Peer group program manual*** (refer to Appendix). Peer leaders will be asked to give a written commitment for taking the role; in return they will get training, a SMART2D Peer leader certificate, a fixed budget for meeting-related expenses, and a small compensation for each group meeting.

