#### 3.3.3.3 Cultural Adaptation and Implementation of Community Strategies in Each Site

Adaptation and implementation of the community strategies across the three countries is described in Table 8. In all the three sites, the community mobilization, and the social support components of peer group program and care companions will be implemented in relatively similar ways and as depicted in the generic model. E.g., it is a relatively common practice for people across the three countries to have significant others as care companions when they visit health facilities. However, there are no systematic procedures or formal guidance for care companion selection or supporting their role in any of the countries. Hence, while care companions will function in both arms, SMART2D will provide guidance and support for the role in the community arm in each country. Furthermore, the care companions will be linked with other community activities such as the peer group meetings. The delivery of the physical environmental support component differs between the countries, with South Africa focusing most on this component and the other two countries implementing it as part of the peer group program. Also, much of the community intervention in South Africa will be delivered by the community care workers, who have a strong role in that setting. Finally, the community linkage is emphasized in Sweden with a multisectorial community link team.

Table 8: Community Strategies as Implemented in the Health Facility + Community Study Arm in the SMART2D study sites

| **COMMUNITY STRATEGIES** | **KEY ELEMENTS** | **South Africa** | **Sweden** | **Uganda** |
| --- | --- | --- | --- | --- |
| **1. Community mobilisation** | a. Messages on lifestyle and diabetes for community members / key stakeholders | Pre-existing:   - Diabetes SA leaflets distributed by SMART2D at community awareness raising event(s) | By SMART2D:   - Brochures on timely care seeking; risk monitoring & screening; healthy lifestyle distributed at different places & events in community | By SMART2D:   - Oral information at household visits for screening purpose |

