| **2. Strengthen support from the environment** | a. Peer group program | By SMART2D:   - Peer group facilitator topic guide & manual for 9 sessions of separate groups for people with pre-diabetes and diabetes | By SMART2D:   - Peer group facilitator topic guide & manual for 9 sessions of separate groups for people with pre-diabetes and diabetes | By SMART2D:   - Peer group facilitator topic guide & manual for 9 sessions of mixed groups with people with pre-diabetes and diabetes |
|  | b. Care Companion (CC) / Healthy Lifestyle Buddy (HLB) involvement | CHWs will take on the task of CC / HLB  Pre-existing:   - PACK CHW guidelines   By SMART2D:   - Skill-enhancement of motivational, behavioural coaching to | CC is a family member, relative, friend, neighbour  By SMART2D:   - Brochure describing CC role and tasks - Identification of CC at facility visit 2 - Invitation to peer groups & activities | CC is a family member, relative, friend, neighbour  By SMART2D:   - CC Guideline for HCW to instruct patient and CC on CC selection and tasks - Identification at month 1(CC) /3 (HLB) - Invitation to HC visits and peer group meetings |
|  | c. Promoting supportive physical environment | By SMART2D:   - Community walks +/- PhotoVoice as part of peer group program | By SMART2D:   - Physical activity and healthy food related activities as part of peer group activities linking with community resources through municipalities / NGOs - Community walks as part of peer group activities | By SMART2D:   - Community walks as an optional activity for peer group |
| **3. Community extension** | a. Community Link Team | By SMART2D:   - Support to CHWs to act as liaison between facility and community. | Pre-existing:   - Citizen Offices with Prevention Coordinators and Citizen Hosts helping citizens and linking them with different public, private and non-governmental organizations and services.   By SMART2D:   - Utilization of the existing networks of Citizens Offices and bringing T2DM on their agenda - Mobilization for recruitment through the network - Linkage of the network with peer groups | By SMART2D:   - Formal introduction meeting between peer leader and facility nurses - Peer leaders to remind peer group participants to go to visits, contact with health facility if loss to follow-up/problems - HCW delivering health education remind participants to attend peer group meetings |

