## 3.6 Recruitment and enrollment of participants

Prior to initiation of the trial, the pre-identified health facility clusters will be randomized either to the facility only, or to the facility plus the community arm al the three country sites; and additional to the current practice arm in Uganda. Each site will screen subjects in their study population to identify potential trial participants, using different algorithms as described below.

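### Community mobilisation belongs to the facility + community arm, yet it is given a recruitment role and delivered at screening before baseline, which does not fit the arm-neutral recruitment in section 3.6

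*Protocol*

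**What the plan says.** **Allocation comes first.** Protocol section 3.6 states: "Prior to initiation of the trial, the pre-identified health facility clusters will be randomized". In Sweden (section 3.6.3) postal-code zones were allocated, and participants are found afterwards by community screening.

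**Mobilisation is an arm-specific strategy.** It is Community Strategy I in Table 6, titled "SMART2D Community Strategies for the Health Facility + Community Arm". The site versions are in Table 8, titled "Community Strategies as Implemented in the Health Facility + Community Study Arm in the SMART2D study sites". The content is active intervention material: awareness of type 2 diabetes and its "prevention and management through healthy lifestyle, timely seeking of care and self-management of the disease".

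**It also serves recruitment and is delivered at screening.** Section 3.3.3.1 says of mobilisation: "It will be used to raise interest in participation in the trial". Of its materials it says: "They will be distributed in the Health Facility + Community arm at community screening events". Table 8 gives the Ugandan form as "Oral information at household visits for screening purpose". For Sweden, a different community-arm element, the Community Link Team, includes "Mobilization for recruitment through the network".

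**Baseline comes last.** Under section 3.7 the baseline evaluation follows enrolment. It covers diet, physical activity, diabetes knowledge, illness perception, self-efficacy and self-regulation, as well as HbA1c.

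**The analysis relies on balance.** Section 3.13.1 expects randomisation to even out baseline differences between arms within each site.

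**The concern.** Randomising clusters protects the comparison only if individuals then enter by the same route in every arm. If one arm's intervention is also one of its recruitment tools, the people who come forward can differ by arm for reasons unrelated to the intervention's effect. Intention-to-treat analysis does not help, because the imbalance arises at entry.

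A second problem is separate from selection. Messages on diabetes and lifestyle given at the screening contact reach one arm before its baseline questionnaires. Perceptions, diet and physical activity are a secondary objective (section 2.2.2) and are analysed as mean change over time (section 3.13.2, item 6). A baseline already shifted in one arm distorts that contrast.

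**Working it through.** No sample size or power figure enters this point, so the check is to set the passages side by side.

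**Order of events in the facility + community arm**
1. Cluster or zone allocated (sections 3.6, 3.6.3).
2. Mobilisation messages given at the screening contact (section 3.3.3.1, Table 8).
3. Eligibility tests, consent, enrolment (section 3.6).
4. Baseline evaluation (section 3.7).

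In the other arms step 2 is absent on the wording of Tables 6 and 8. Section 3.6 neither gives control clusters equivalent messages nor holds mobilisation back until after step 4.

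**Site by site: recruitment section against Table 8**
- *Uganda.* Section 3.6.1 describes leader meetings and radio across both districts, then field assistants visiting households in every cluster, with entry depending on repeated fasting glucose tests. That leaves limited room for differential recruitment. Table 8, however, places the arm's oral messages at those same household visits, so exposure before baseline is explicit.
- *South Africa.* Section 3.6.2 describes an awareness campaign at a central venue to drive recruitment and names no arm. Table 8 lists leaflets at awareness events as a facility + community strategy. Either only one arm is mobilised, or the controls receive part of the component under test.
- *Sweden.* Section 3.6.3 describes outreach and screening in public places, with people who test positive sent to whichever arm applies. Table 8 puts brochures on screening and lifestyle, and recruitment through the network, under the facility + community arm. Attendance at screening is voluntary, so differential recruitment is most plausible here.

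**Length of exposure before baseline**
- Table 15 places screening at -7 to 0 days, so exposure that starts at the screening contact lasts about a week or less at enrolment.
- The data collection instructions recommend splitting baseline in two, with self-efficacy, self-regulation and knowledge asked when the pedometer is collected after 7 days. For those items exposure could be about 7 + 7 = 14 days.
- The planned timeline (appendix 5.1) shows enrolment from January to November 2017, which is 11 months. Section 3.3.3.1 also spreads the material through partner organisations, peer groups and the link team, so late enrollees in that arm could have been exposed for longer.

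**Scope for adjustment**
- Section 3.10 gives 9 clusters in Uganda (three arms), 2 in South Africa and 4 in Sweden (two arms each). With equal allocation that is 9/3 = 3, 2/2 = 1 and 4/2 = 2 clusters per arm.
- The natural covariates for motivation (knowledge, self-efficacy, self-regulation) are measured after the exposure, so the intervention may already have altered them.

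**The case against.** The strongest reply is that section 3.6 governs who enters the trial, and it describes the same recruitment in every arm. On that reading mobilisation merely accompanies screening. The Swedish network entry may refer to the general municipal outreach of section 3.6.3, and the Ugandan entry gives no content beyond its row label. This stands in part: different recruitment by arm is a consequence of sections 3.3.3.1 and 3.3.3.3 as written, not something the protocol reports. It does not remove the conflict, because those sections assign both the recruitment purpose and delivery at screening to one arm.

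A second reply is that mobilisation is a community-level activity, that access to care is part of the general objective (section 2.1), and that it cannot be switched on person by person. That is right, and it limits the remedy to what is said and handed out at screening contacts.

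Three stronger readings are tempting but unsupported:
- *The bias favours the facility + community arm.* A reader might infer this from more motivated volunteers. Outreach could equally bring in less engaged people, and exposure before baseline may shrink measured change. The direction is open.
- *The bias is a given share of the target effect.* An assumed shift of 0.5 to 1 mmol/mol has no source in the document. The target is also stated two ways: 3 mmol/mol in the text of section 3.10 (0.5/3 to 1/3, or 17% to 33%) and 5 mmol/mol in Table 16(a) (0.5/5 to 1/5, or 10% to 20%).
- *Adjustment is useless.* The pre-diabetes primary outcome is change from baseline (section 3.9), and section 3.13.1 refers to accounting for baseline differences. That may help, but it cannot be relied on.

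**Conclusion.** The point holds as an inconsistency with a plausible route to bias. Section 3.3.3.1 and Table 8 give an arm-specific intervention a recruitment purpose and deliver it at screening, after allocation and before baseline. Section 3.6 describes arm-neutral recruitment. They must be reconciled.

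If sections 3.3.3.1 and 3.3.3.3 are followed as written, two things follow. Recruitment can differ by arm, most plausibly in Sweden and least in Uganda. And one arm's baseline knowledge, perceptions and behaviour are measured after exposure to intervention messages. For South Africa the protocol leaves open whether one arm is mobilised or the controls are exposed as well.

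Neither the size nor the direction of the bias can be derived from the document. Exposure limited to the screening window is unlikely to change baseline HbA1c, so for the primary outcomes the concern is selection. Exposure before baseline mainly threatens the secondary perception and behaviour outcomes. The conclusion assumes that Tables 6 and 8 mean what their titles say, namely that these strategies belong to the facility + community arm only.

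**What to change.** 1. Use one arm-neutral sensitisation, recruitment and screening script, with the same materials, in all arms at each site.
2. Remove the recruitment purpose from Community Strategy I and the recruitment entry from the Swedish network element.
3. Give no arm-specific mobilisation messages at screening events or screening household visits. Give them to participants once their baseline assessment is complete, including the second baseline visit where it is split. Wider community-level activities may continue as part of the intervention.
4. For South Africa, state which arm the awareness campaign serves and bring section 3.6.2 and Table 8 into line.
5. Report numbers approached, screened, eligible and consenting by cluster and arm, so that differential recruitment can be seen.

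The cost is a common script and re-timed materials, with no change to the sample size. Participants in the facility + community arm receive the messages slightly later, and that arm may attract fewer volunteers. Community-level activity that continues during the 11 months of enrolment can still reach later enrollees, so item 3 reduces exposure before baseline without removing it.

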#### 3.3.3.2 Training for Community Strategies

Table 7 outlines all the training activities required to deliver the generic community strategies. Most strategies are linked with peer group activities or facility care, hence training of peer leaders and health care workers (MC) includes training for these strategies as well.

***Peer group training*** protocol includes a training workshop for peer leaders for getting the peer group started, and further training and mentoring workshops or short sessions according to need to support the conduct of further meetings, guiding of the community walks, utilization of the CC and maintaining linkages with the facility. Resource materials include a ***Peer Group Guidelines*** document, and a ***Short*** ***Guide to Peer Leader Behaviors***, consisting of rapport building and autonomy supportive behaviors.

***Care Companion training.*** Instead of separate training program for Care Companions / Healthy Lifestyle Buddies, introduction and/or support for their role in the Health Facility + Community study arm will be integrated into other activities in the intervention:

1. Motivational coaching group visits at the health facility, to which they will be asked to accompany the individuals with pre-diabetes/diabetes.
2. Peer group meetings to which they will have open invitations.

***Training for Community Extension*** is integrated with the peer leader training, and with the HCW training program.

Table 7: Training and Supervision/Mentoring for Implementation of Community Strategies

| **COMMUNITY STRATEGIES** | **KEY ELEMENTS** | **TRAINING & SUPERVISION / MENTORING** |
| --- | --- | --- |
| **I. Community mobilization** | a. Messages on lifestyle and diabetes for community members / key stakeholders | No separate training required |
|  |  |  |
|  |  |  |
| **II. Strengthen support from the environment** | a. Patient peer group program | Training:   - One day skill-building workshop for peer leaders to get groups started: |
|  |  | - - Peer group principles and facilitation   - Peer group portfolio for themes and activities   - Practical organization of peer group |
|  |  | Mentoring:   - Half-a-day maintenance workshop/s for peer leaders to share and learn - Short mentoring sessions (f2f or group TC) |
|  | b. Care Companion (CC) / Healthy Lifestyle Buddy (HLB) involvement | No separate training for CC   - Training for conducting CC introduction as part of the MC session at facility integrated to HCW training - CC support integrated to PL training |
|  | c. Promoting supportive physical environment | Community walk overview as part of peer leader training |
| **III. Community extension** | a. Community Link Team | Training:   - Half-a-day introductory and skill building workshop   Mentoring:   - Short mentoring sessions (f2f or group TC) - Half-a-day closing workshop for evaluation and maintenance |

#### 3.3.3.3 Cultural Adaptation and Implementation of Community Strategies in Each Site

Adaptation and implementation of the community strategies across the three countries is described in Table 8. In all the three sites, the community mobilization, and the social support components of peer group program and care companions will be implemented in relatively similar ways and as depicted in the generic model. E.g., it is a relatively common practice for people across the three countries to have significant others as care companions when they visit health facilities. However, there are no systematic procedures or formal guidance for care companion selection or supporting their role in any of the countries. Hence, while care companions will function in both arms, SMART2D will provide guidance and support for the role in the community arm in each country. Furthermore, the care companions will be linked with other community activities such as the peer group meetings. The delivery of the physical environmental support component differs between the countries, with South Africa focusing most on this component and the other two countries implementing it as part of the peer group program. Also, much of the community intervention in South Africa will be delivered by the community care workers, who have a strong role in that setting. Finally, the community linkage is emphasized in Sweden with a multisectorial community link team.

Table 8: Community Strategies as Implemented in the Health Facility + Community Study Arm in the SMART2D study sites

| **COMMUNITY STRATEGIES** | **KEY ELEMENTS** | **South Africa** | **Sweden** | **Uganda** |
| --- | --- | --- | --- | --- |
| **1. Community mobilisation** | a. Messages on lifestyle and diabetes for community members / key stakeholders | Pre-existing:   - Diabetes SA leaflets distributed by SMART2D at community awareness raising event(s) | By SMART2D:   - Brochures on timely care seeking; risk monitoring & screening; healthy lifestyle distributed at different places & events in community | By SMART2D:   - Oral information at household visits for screening purpose |
| **2. Strengthen support from the environment** | a. Peer group program | By SMART2D:   - Peer group facilitator topic guide & manual for 9 sessions of separate groups for people with pre-diabetes and diabetes | By SMART2D:   - Peer group facilitator topic guide & manual for 9 sessions of separate groups for people with pre-diabetes and diabetes | By SMART2D:   - Peer group facilitator topic guide & manual for 9 sessions of mixed groups with people with pre-diabetes and diabetes |
|  | b. Care Companion (CC) / Healthy Lifestyle Buddy (HLB) involvement | CHWs will take on the task of CC / HLB  Pre-existing:   - PACK CHW guidelines   By SMART2D:   - Skill-enhancement of motivational, behavioural coaching to | CC is a family member, relative, friend, neighbour  By SMART2D:   - Brochure describing CC role and tasks - Identification of CC at facility visit 2 - Invitation to peer groups & activities | CC is a family member, relative, friend, neighbour  By SMART2D:   - CC Guideline for HCW to instruct patient and CC on CC selection and tasks - Identification at month 1(CC) /3 (HLB) - Invitation to HC visits and peer group meetings |
|  | c. Promoting supportive physical environment | By SMART2D:   - Community walks +/- PhotoVoice as part of peer group program | By SMART2D:   - Physical activity and healthy food related activities as part of peer group activities linking with community resources through municipalities / NGOs - Community walks as part of peer group activities | By SMART2D:   - Community walks as an optional activity for peer group |
| **3. Community extension** | a. Community Link Team | By SMART2D:   - Support to CHWs to act as liaison between facility and community. | Pre-existing:   - Citizen Offices with Prevention Coordinators and Citizen Hosts helping citizens and linking them with different public, private and non-governmental organizations and services.   By SMART2D:   - Utilization of the existing networks of Citizens Offices and bringing T2DM on their agenda - Mobilization for recruitment through the network - Linkage of the network with peer groups | By SMART2D:   - Formal introduction meeting between peer leader and facility nurses - Peer leaders to remind peer group participants to go to visits, contact with health facility if loss to follow-up/problems - HCW delivering health education remind participants to attend peer group meetings |

